## Methods

### Aim and research question

This project aims at developing an Internet-based treatment for BED based on evidence-based CBT [39].

The primary goal is to test the feasibility and suitability of the program and to evaluate the treatment outcome (short-term and long-term) in comparison to a pure and a placebo-inspired waitlist control group (CG) (i.e. reduction of binge-eating episodes and ED pathology as primary outcome variables). We expect that the immediate treatment group (TG) shows a significantly larger improvement in treatment outcomes during the first four weeks of treatment compared to the combined pure and placebo-inspired CGs during the first four weeks of the waiting period. We further expect that all three groups exhibit comparable temporal courses of treatment outcomes in the short (during eight weeks of active treatment) and long term (during the six months of follow-up). Thus, we expect that the placebo-inspired CG shows no advantage in terms of treatment outcome compared to the pure CG and the TG during the treatment and/or the follow-up phase. Our secondary goal deals with moderators and mediators of treatment outcome such as commitment, emotion and impulse regulation capacities, body image or interpersonal problems, depressive symptoms, and level of functioning.

The third goal of this study is to indirectly compare the present Internet-based treatment data with available data from: (1) a face-to-face therapy (group and single setting) in which the same therapeutic approach has been applied [12, 14]; and (2) from a conventional GSH program with a book relying on the same therapeutic concept [38].

The fourth goal is to explore the usability and acceptance of the program in order to gain information about users’ needs and specificities to improve interfaces of Internet-based treatments for vulnerable user groups such as patients with a mental disorder. We evaluate treatment integrity of therapists and treatment adherence of patients in order to increase the internal validity of our findings. The contents of the written feedback of the therapists are evaluated and we rate their fidelity with treatment guidelines. Patients’ compliance with the treatment is assessed using measures such as the time they spent with the program and by the number of exercises which are edited according to treatment suggestions.

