### Material and measures

The content of the eight sessions and three follow-up sessions is all derived from established and evaluated treatment material [12–15, 39, 48, 49].

In Table 1, an overview of the main contents of each session is given.

**Table 1 Tab1:** Main content of therapy sessions

Session	Content
0	Introduction to the program
1	Individual etiological model of BED
	Self-observation of eating behavior
2	Motivation
	Goal attainment scale
3	Regular eating
	Analyzing binge-eating episodes with the ABC-model
4	Developing strategies to overcome binge-eating (trigger and reaction control)
5	Positive/enjoyable activities
	Working with emergency cards
6	Expanding strategies
	Dysfunctional thoughts
7	Dysfunctional thoughts and body image
	Reduction of overweight
8	Setting longer-term goals
	Coping with future difficulties
	Relapse prevention
Follow-up sessions 1–3	Further goals
	Coping with current difficulties
	Relapse prevention

Table 2 gives an overview of all instruments that will be applied during the study. Primary outcome variables are number of binge-eating episodes and ED pathology. Secondary outcome variables are reduction of depressive symptoms and increase of the level of functioning. Moreover, all exercises that the patients edited during the sessions as well as all communication between the therapist and the patients will be stored and evaluated (e.g. regarding treatment integrity).

**Table 2 Tab2:** Instruments

Instrument	Description/Construct	Time point
Interviews		
Diagnostic interview for psychiatric disorders, short version (Mini-DIPS; [53])	Structured interview to assess psychiatric disorders according DSM-5. Duration: approx. 45 min.	t_1_, t_2_
Eating Disorder Examination (EDE; German version [54])	Structured interview to assess eating disorder pathology Duration: approx. 45 min.	t_1_
Therapists ratings		
Clinical global impression scale [55]	Measure of symptom severity, treatment response and the efficacy of treatments in patients with mental disorders. 7 items rated by the clinician.	t_1_, t_2_
Self-report questionnaires		
Sociodemographic questions (own items)	Sociodemographic questions (gender, age, nationality, sick leave days, prior treatments etc.). 35 items.	t_1_
Patient’s expectancies regarding the therapy (own items)	Questions to assess attitude and expectations of the patients towards the internet-based treatment. 5 items.	t_1_

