### Statistical analysis

In model 1 we test whether treatment outcomes improve during the active treatment phase across (i.e. pooled for) all three groups to test for the overall efficacy of the GSH program. This model thus contains one within-subjects factor (pre-post). In model 2 we test whether the temporal course of GSH program’s outcomes during active treatment and during follow-up varied among the three groups (TG, CG1, and CG2). We will apply a two-way mixed analysis of variance with group (three levels) as between-subjects and time (pre-post or post-follow-up) as within-subjects factors, whereby we are interested in the interaction between group and time.

Power analyses: based on prior research data (e.g. [25]), we expect an 18% dropout rate for our power estimations. The correlation (rho) of the number of weekly binges between the two time points is estimated to be around 0.6 (using data published in [14]). Here we assume a slightly more conservative value of rho = 0.5. Based on alpha = 0.05 (two-sided), beta = 0.2, a medium effect size (Cohen’s f = 0.25), and a dropout rate of 18%, the estimated sample size is 34 based on model 1 and 42 (14 per group) based on model 2. Taking the larger of these two values (42) this value was subsequently increased to 60 (20 per group) to be on the safe side with respect to the required sample size.

Analyses based on the secondary goal will include moderators and mediator models.

Analyses for the third (compare the present Internet-based treatment with available data from a face-to-face therapy and conventional GSH program with a book) and fourth goal (explore usability) are of exploratory nature and will thus use descriptive statistics such as means, standard deviations, and percentages.

Multilevel models will be used to analyze the data of the first and second goals [50], including multilevel structural equation models (for mediator models in second goal [51]).

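### The only randomised treated-versus-untreated comparison (TG against the combined control groups over four weeks) has no model or sample size, and overall efficacy is assigned to an uncontrolled pre-post change

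*Protocol article*

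**What the plan says.** All places are in the Methods of the protocol article.

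- **Aim and research question.** The primary goal includes evaluating outcome ("short-term and long-term) in comparison to a pure and a placebo-inspired waitlist control group"). The first expectation is that "the immediate treatment group (TG) shows a significantly larger improvement in treatment outcomes during the first four weeks of treatment compared to the combined" control groups over their four-week wait. The second concerns the time after that: "We further expect that all three groups exhibit comparable temporal courses of treatment outcomes in the short (during eight weeks of active treatment"), and likewise during six months of follow-up.
- **Control groups (CG).** Both control groups wait four weeks and then start the program. During the wait they report binge-eating episodes and mood.
- **Statistical analysis, model 1.** Its stated question: "treatment outcomes improve during the active treatment phase across (i.e. pooled for) all three groups to test for the overall efficacy of the GSH program". Its only factor is pre-post.
- **Statistical analysis, model 2.** A group-by-time analysis of variance asks whether outcomes "during active treatment and during follow-up varied among the three groups (TG, CG1, and CG2"). Time is either pre-post or post-follow-up, and the interaction is the effect of interest.
- **Statistical analysis, power.** 34 patients for model 1 and 42 for model 2, raised to 60 (20 per group).
- **Statistical analysis, last sentence.** Multilevel models will be used for the first and second goals. No contrast or time window is named.
- **Material and measures.** "Primary outcome variables are number of binge-eating episodes and ED pathology". Table 2 lists the Weekly Binges Questionnaire (WBQ) weekly during waiting and treatment, and the EDE-Q at t1, t2 and t3.

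**The concern.** Randomisation buys one thing here that a single-arm study could not: a comparison, over four weeks, of patients who have the program with patients who do not. After week 4 every arm is being treated or has been treated. The plan names that comparison first among its expectations, yet the models it fixes, and the calculation that justifies its size, are for other questions.

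The label on model 1 makes this more than an omission. People enter a binge-eating trial when symptoms are high, and all of them record their binges weekly. Some fall in episodes is therefore expected without any program effect. A pooled pre-post change contains that fall and has nothing to subtract it with. If model 1 is reported as the efficacy test, the program is credited with all of the change, and the stated 80% power refers to that test rather than to the randomised question.

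**Working it through.** **1. Does either model contain the contrast?**

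| | First expectation | Model 1 | Model 2 |
|---|---|---|---|
| Groups | TG vs CG1 + CG2 combined | all pooled | three separate groups |
| Period | first four weeks: TG treated, CGs waiting | active treatment | active treatment; follow-up |
| Untreated comparator | yes | none | none |
| Expected result | difference | improvement | no difference between groups |

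Neither model includes the waiting period, a four-week window or the combined control group. Model 2 also looks for an interaction that the aims section expects to be absent.

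**2. Reproducing the plan's sample sizes.** Inputs from Statistical analysis: f = 0.25, rho = 0.5, two time points (m = 2), two-sided alpha 0.05, power 0.80. The noncentrality is lambda = N·m·f²/(1 − rho) = N × 2 × 0.0625/0.5 = 0.25N.

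- Model 1, F with (1, N − 1) df: N = 34 gives power 0.808.
- Model 2 interaction, F with (2, N − 3) df: N = 42 gives power 0.803.

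Both figures match, so they belong to these two models. As a side note, they match only without a dropout allowance. Dividing by 0.82 gives 34/0.82 = 41.5, so 42, and 42/0.82 = 51.2, so 52. The planned 60 absorbs this: about 49 remain after 18% dropout (60 × 0.82 = 49.2), where model 2 has power of about 0.87.

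**3. What 60 patients give for the omitted contrast.** Two-sample t-test on change scores, TG against combined CGs, noncentral t with noncentrality d/√(1/n₁ + 1/n₂). Here d is the difference in mean change divided by the SD of change. That SD is sigma·√(2(1 − rho)), which equals sigma at rho = 0.5. Allocation of 20:20:20 makes the contrast 20 vs 40, or about 16 vs 33 after 18% dropout.

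The plan gives no d for this contrast, so d is an assumption, shown as a range:

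| d | Power, 20 vs 40 | Power, 16 vs 33 |
|---|---|---|
| 0.5 | 0.44 | 0.36 |
| 0.8 | 0.82 | 0.73 |
| 1.0 | 0.95 | 0.90 |
| 1.06 | 0.97 | 0.93 |

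The smallest d with 80% power is 0.78 for 20 vs 40 and 0.87 for 16 vs 33.

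**4. Carrying over the plan's own effect size.** With lambda = 0.25N, the effect on the change-score scale is f = √0.25 = 0.5. For two equal groups, d = 2 × 0.5 = 1.0. For a 1:2 split, f² = (1/3)(2/3)d², so d = 0.5/√(2/9) = 1.06. Power after dropout is then about 0.90 to 0.93.

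**The case against.** The strongest reply is that the contrast is described, only not in the statistics section. The aims give its groups, window, direction and outcomes, and the last sentence of Statistical analysis promises multilevel models for the first goal, to which it belongs. The article condenses a fuller protocol that is not shown, and it speaks of a primary goal and expectations, not of a primary hypothesis.

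Part of this stands. It cannot be said that the comparison will go unanalysed. But the multilevel sentence names a method, without a contrast, window or comparator. The article also does more than leave detail out: it gives the efficacy test to a model without a comparator and sizes the trial on models that do not contain the randomised question.

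Three stronger readings are tempting, and the document does not support them:

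- **That the trial is underpowered.** The 36% power at d = 0.5 rests on an effect that the plan does not state. Its own f and rho, carried over, give about 0.90 to 0.93.
- **That the long-term comparison is impossible and should be deleted.** It can be read as comparing the courses of the three randomised arms through treatment and follow-up, which model 2 does. It is not a comparison with untreated patients, but it is legitimate.
- **That two primary outcomes and several models inflate the error rate to a definite figure.** The plan does not list the tests such a figure would need, and a multiplicity rule is commonly left to the SAP.

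**Conclusion.** The point holds as a mismatch between aim and analysis. The four-week comparison of TG with the combined control groups is the only randomised treated-versus-untreated contrast, neither fixed model tests it, and neither 34 nor 42 was derived for it. Calling model 1 the test of overall efficacy is wrong for a model without a comparator.

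In size, 60 patients give 80% power for a standardised difference in change of about 0.78 with everyone evaluable and about 0.87 after 18% dropout. These values assume a two-sided 0.05 test on change scores and 1:2 allocation; in units of the outcome SD they also assume rho = 0.5. Whether that is adequate depends on an effect the plan does not give, so the conclusion is that the sample size is unjustified for this contrast, not that it is too small.

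One matter is open. The EDE-Q is listed only at t1, t2 and t3, and waiting-period measurement is described as binge episodes and mood. ED pathology may therefore have no week-4 value. The text does not define the time points and the schedule figure is not shown, so this needs confirming.

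**What to change.** In Statistical analysis:

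1. Specify a between-group model for TG against the combined control groups over weeks 0 to 4 from randomisation, in all randomised patients, on weekly binge-eating episodes (WBQ), and name it as the efficacy test.
2. Relabel model 1 as a description of within-group change during treatment, and remove the claim that it tests overall efficacy.
3. State the detectable effect for the contrast at 1:2 allocation: about 0.78 for 20 vs 40, and about 0.87 for 16 vs 33 after 18% dropout. Say which effect is expected and why.
4. Confirm whether ED pathology is measured at week 4 before including it in this contrast. If it is not, say that the four-week comparison covers binge-eating episodes only.

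Model 2 can stay for the courses during treatment and follow-up.

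The cost is one extra model on data already collected, since the WBQ is completed weekly during both waiting and treatment. No further patients or visits are needed. The drawback for the authors is a weaker label for model 1.

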
Alongside the advantages of Internet-based programs, there are also caveats such as dropout rates with high variances of 5–77%, whereas compliance was enhanced by pretreatment face-to-face assessments and therapists guidance through emails. These preliminary findings are of importance, as compliance was associated with better outcomes regarding the reduction of ED symptomatology [11, 22, 29, 30]. In a review, Schlegl et al. [24] found evidence for the efficacy of guided computer and Internet-based interventions, somewhat less for AN and more for patients with BN. They emphasized that further research is needed to understand the optimal level of therapist guidance in terms of frequency and quality. The question of the professional level of the guides and the efficacy of such programs also needs to be evaluated in comparison with face-to-face or blended treatments. Furthermore, research should address predictors and mediators of treatment outcomes.

The present randomized controlled trial (RCT) adds to existing data on treatment efficacy of Internet-based treatments for BED as the duration of treatment is shorter and additionally the effect of two waitlist conditions is evaluated. The first group is a pure waitlist control group (CG 1), where patients receive short weekly messages with a link to a short questionnaire to assess the number of weekly binges but no additional information during the four weeks of waiting time. The second group is a placebo-inspired control group (CG 2) that is provided with weekly messages with the aim to induce positive expectations regarding the program and to establish a therapeutic relationship with the therapist. This group is based on previous evidence from psychotherapy research referring to the effect of positive expectation on treatment adherence, therapeutic relationship, and dropout rate and treatment success [31–36]. Inspired by research on depressive disorder [37], this study will attempt to actively induce placebo in terms of positive expectation effects. To our knowledge, this is the first time this technique will be used in BED research. It will allow us to investigate the influence of positive expectations on treatment outcome in BED in more detail. The placebo inspired CG will allow rigorous examination of the presumably efficient disorder specific treatment that is applied in this study, since the specific active treatment is comparable to the unspecific placebo intervention.

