### Procedure

Altogether the active treatment phase including pre and post-diagnostic lasts approximately 11 weeks (plus four weeks in the control groups). The three follow-up sessions take place one, three, and six months after the last session of the active treatment. All exercises are an integral part of the sessions and mandatory. The patients are invited to work on the different exercises on an individual basis also between sessions.

Each patient is accompanied and guided by one of seven therapists that received a specific training in delivery of the current Internet-based treatment. All therapists are postgraduate psychologists or psychotherapists at the Center for Psychotherapy at the University of Fribourg and are continuously supervised by the study leaders (SM, AW). The therapists provide a weekly written feedback on the exercises via a communication system that is built into the GSH program. Patients can proceed to the next session after completing all parts of the current session along with the related exercises. The next session will then be unlocked for the patient. After finishing a session, patients will have to wait 7–10 days before they can proceed with the next session.

Since dropouts are a major problem in Internet-based treatments for EDs (up to 77%), our GSH program features several measures to support the compliance: a continuous personal contact to a therapist (face-to-face or telephone diagnostic assessment at the beginning of the program and messaging through the build-in communication system during the following three days after each session’s completion); a clear structure of the program (which has been shown to be beneficial in BED self-help programs) (e.g. [23]); and a conjoint scheduling. In addition, the introductory session provides patients with all necessary information to work smoothly through the program. Finally, the first two sessions include several interventions to develop and maintain sustained motivation. Altogether, this procedure aims at supporting the working alliance which has been positively related with the outcome in Internet-based treatments for BED [47].

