### Control groups (CG)

After having given informed consent, patients are randomly assigned to the TG (immediate start with the treatment) or either of the CGs. The waiting time in CG 1 (pure waitlist group) and CG 2 (placebo-inspired waitlist group) lasts four weeks. CG 2 will receive standardized weekly messages during their four-week waiting period. These messages include induction of positive expectations regarding program participation, a summary of the current evidence of BED treatment and benefits of such a standardized, evaluated treatment, quotes from former patients, and motivating words. This information does not contain any form of deception. The pure waitlist group will wait exclusively for four weeks. Both CGs fill in a short questionnaire to assess core BED symptomatology (i.e. binge-eating episodes) and to monitor changes in mood. After the waiting period, patients of both CGs start with the Internet-based GSH program.

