The efficacy, usability, and adoption of the developed program will be evaluated through interviews, questionnaires, and analysis of interaction logs. In respect of psychotherapy research, the present study provides the possibility of examining the efficacy of a standardized disorder-specific treatment programm in comparison to a pure waiting period and a placebo-inspired intervention. Even if we make the rather conservative assumption that the specific intervention during active treatment is the “verum” that results in positive outcome and the “placebo” is not effective, we could nevertheless assume that the placebo-inspired CG shows advantages in terms of a faster positive development during treatment due to higher positive expectations and a more established therapeutic relationship already at the beginning of the active treatment. Such a result would refer to an “add-on effect” of a placebo-inspired waiting period or in other words of a preparation phase before a disorder-specific treatment, which would be relevant for clinical practice. The comparison of the present GSH program with established face-to-face therapy and a book-based GSH program, as well as the investigation of moderating and mediation variables, will improve the understanding of differential indications in BED treatment.

This research will also help to understand the specific interaction traits of users following an Internet-based treatment and to gather requirements for user interfaces that support their needs and reduce the risk of therapy drop-out. Another expected contribution of this research in the field of human–computer interaction is the exploration of mechanisms to adapt automatically the content or alerts of the therapy according to the patient specificities, towards user-induced adaptation [52] and personalized therapy.

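### The four-week hypothesis merges the pure and placebo-inspired waitlists, so a significant result would not show an advantage over the placebo-inspired arm

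*Protocol article*

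**What the plan says.** In the protocol article, Aim and research question names a pure and a placebo-inspired waitlist as the comparators for treatment outcome. It then states one between-group superiority hypothesis, for the first four weeks. The improvement in TG is expected to be significantly larger, and the reference is the two control groups taken together: "compared to the combined pure and placebo-inspired CGs during the first four weeks of the waiting period".

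Two other sections say what the placebo-inspired arm is for:

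- Background: "The placebo inspired CG will allow rigorous examination of the presumably efficient disorder specific treatment", and the reason given is "since the specific active treatment is comparable to the unspecific placebo intervention".
- Discussion: the study offers the possibility of "examining the efficacy of a standardized disorder-specific treatment programm in comparison to a pure waiting period and a placebo-inspired intervention".

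Control groups (CG) sets the wait at four weeks for both control groups, after which both start the same programme. During the wait, "CG 2 will receive standardized weekly messages during their four-week waiting period".

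Statistical analysis describes two models. Model 1 tests pre-post change over active treatment, pooled over all three groups. Model 2 tests the group-by-time interaction with three groups, during active treatment and during follow-up. The section adds in general terms that multilevel models will be used for the first and second goals.

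**The concern.** The four-week wait is the only time when the programme and the placebo messages run side by side. After it, every arm receives the programme. A comparison of treatment with the placebo-inspired condition therefore has to come from those four weeks, and the one hypothesis stated for that period averages the two control groups.

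An average over two controls answers a question about their mixture. If the messages have some effect, the merged estimate is smaller than the effect over pure waiting and larger than the effect over the messages. A significant merged result could then be reported, in the terms used in Background and Discussion, as if treatment had been shown to work beyond placebo, when that comparison was never tested.

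**Working it through.** **1. The plan's own figures.** Inputs from Statistical analysis: Cohen's f = 0.25, rho = 0.5, two-sided alpha 0.05, power 80%, two time points (m = 2). The noncentrality is λ = f²·N·m/(1 − rho).

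- Model 1: λ = 0.0625 × 34 × 2/0.5 = 8.5 with df 1 and 33. Power is 0.808, so N = 34 is reproduced.
- Model 2: λ = 0.0625 × 42 × 2/0.5 = 10.5 with df 2 and 39. Power is 0.803, so N = 42 is reproduced.

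Both figures match without a dropout allowance. Neither calculation concerns a four-week contrast between TG and a control group.

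**2. Which stated analysis covers which period**

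| Analysis | Period | Separates TG from CG 2? |
|---|---|---|
| Four-week hypothesis | TG weeks 1–4, control groups waiting | No, control groups merged |
| Model 1 | Active treatment | No, all groups pooled |
| Model 2 | Active treatment, follow-up | Yes, but all groups have the programme |

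**3. What the merged contrast estimates.** Let TG's four-week change exceed that of CG 1 by d, and let CG 2 achieve a fraction q of that advantage. Then

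TG − (CG 1 + CG 2)/2 = d − qd/2 = d(1 − q/2).

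- q = 0 (messages inert): d, which equals both TG − CG 1 and TG − CG 2.
- q = 0.5: 0.75d, while TG − CG 1 = d and TG − CG 2 = 0.5d.
- q = 1 (messages match the programme): 0.5d, while TG − CG 2 = 0.

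**4. Standard errors.** The unit is the SD of the change. With rho = 0.5 its variance is 2σ²(1 − 0.5) = σ², so it equals the raw SD. Using rho = 0.5 for the four-week change is an assumption. With 20 per arm:

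- Merged: √(1/20 + 1/40) = 0.274.
- Pairwise: √(1/20 + 1/20) = 0.316.
- Ratio: 0.316/0.274 = 1.15.

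**5. Chance of a significant merged result when TG = CG 2 (q = 1).** Noncentral t, two-sided 0.05, three-arm error with df = 57 (20 per arm) or 45 (16 per arm). For 20 per arm the noncentrality is (d/2)/0.274. The values of d are assumptions, because the article gives no four-week effect against either control. Sixteen per arm is roughly 20 × 0.82 = 16.4.

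| d (SD) | True merged contrast | 20 per arm | 16 per arm |
|---|---|---|---|
| 0.8 | 0.4 | 30% | 25% |
| 1.0 | 0.5 | 43% | 36% |
| 1.2 | 0.6 | 58% | 48% |

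A direct two-sided TG versus CG 2 test would reject 5% of the time in each row, 2.5% in favour of TG.

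In a milder case (q = 0.5, d = 1.0, 20 per arm), the merged test is significant 77% of the time and the direct TG versus CG 2 test 34%.

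**6. What separate contrasts can deliver.** TG versus CG 2 at 20 per arm has 34% power for a true difference of 0.5 SD and 70% for 0.8 SD. At 16 per arm these fall to 28% and 60%. The difference detectable with 80% power is 0.90 SD, against 0.78 SD for the merged contrast. At 16 per arm the values are 1.01 and 0.88 SD.

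**The case against.** **CG 2 has other purposes.** Background also gives it the task of studying positive expectations, the Discussion raises a possible add-on effect of a preparation phase, and the Abstract calls the expectation question preliminary. Model 2 keeps the three groups apart for those questions. This stands: merging does not waste the third arm. It still leaves unanswered the comparison with a placebo-inspired condition that the article also promises.

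**The percentages are not error rates.** With d above zero the merged null hypothesis is false, and rejecting it is correct. They also assume that messages alone match the whole programme over four weeks, which nothing in the article supports. Both remarks stand, and the figures serve only as an illustration. If the messages are inert, the merged contrast estimates both differences without bias and more precisely. The article offers an inert placebo only as a conservative assumption, though, and its no-advantage expectation for CG 2 concerns treatment and follow-up, not the wait.

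**Merging is openly stated and saves power.** In a trial of 60 this is a defensible choice for the leading test, so there is no case for removing it.

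**The full protocol is not shown.** It may contain pairwise contrasts. The point therefore rests on the hypothesis as written here set against the claims as written here.

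**A stronger reading is tempting but unsupported.** A reader might take Background to say that the two conditions are matched for attention, and object that the programme brings exercises while "The therapists provide a weekly written feedback on the exercises via a communication system that is built into the GSH program". The word used there most naturally means that the two can be compared. The article never claims matching, and it describes openly what each arm receives.

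**Conclusion.** The point holds as a mismatch between claim and contrast. The article says efficacy is examined "in comparison to a pure waiting period and a placebo-inspired intervention", yet the one four-week between-group hypothesis merges the two, and neither model covers the wait. A significant merged result would support superiority over the mixture of the control groups, not over the placebo-inspired arm.

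That conclusion follows from the form of the contrast and needs no assumption about effect size. The illustrated size (30% at 0.8 SD, 43% at 1.0 SD) does rest on assumptions: CG 2 improving as much as TG, the chosen values of d, 20 per arm and no dropout.

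A reader might infer that the leading test is invalid or has an inflated error rate. It does not: it is a valid test of a different question. The problem lies in what may be concluded from it, and a modest change cures it.

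**What to change.** In Aim and research question, keep the merged contrast as the leading four-week test if wanted. Beside it, state TG versus CG 1 and TG versus CG 2 as separate pre-specified four-week contrasts, each with a confidence interval, for each primary outcome. In Statistical analysis, name the model that covers the waiting period, since models 1 and 2 do not. In Background and Discussion, base any statement about efficacy beyond placebo on TG versus CG 2 only.

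The cost is wording and two further contrasts, with no new arms or patients. Table 2 lists the weekly binge questionnaire for both the wait and treatment, so binge frequency is available at four weeks. It lists the EDE-Q at t1, t2 and t3. The schedule figure is not shown, so the authors should confirm which four-week measurement serves eating-disorder pathology.

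The price in precision is real. Each separate contrast has a 15% larger standard error (0.316 versus 0.274 SD), and TG versus CG 2 has about 34% power at 0.5 SD and 70% at 0.8 SD with 20 per arm. It should be reported as an estimate with its interval, and a non-significant result should not be read as equivalence of treatment and placebo messages.
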